## Abstract

**Background:**

Spinal pain is a highly prevalent condition affecting a large part of the population. Chiropractic maintenance care (MC) is a management strategy intended to prevent spinal pain recurrent episodes and deterioration by treating patients at pre-planned intervals. A previous study showed that patients identified as a dysfunctional subgroup by the West Haven-Yale Multidimensional Pain Inventory (MPI) and receiving MC had fewer days with bothersome LBP. This suggests MC may have superior effectiveness in this subgroup of patients. The MPI, however, is not practical for daily clinical practice, prompting the development of the MAINTAIN instrument. This study aims to (1) assess the effectiveness and cost-effectiveness of stratified MC using the MAINTAIN instrument, and (2) assess the fidelity and procedure compliance of implementing the MAINTAIN instrument.

**Methods:**

This pragmatic randomized clinical trial will recruit 225 consecutive patients (18–65 years old) with significant (> 30 days in the past 12 months) recurrent spinal pain presenting to chiropractic clinics. After the initial 3 weeks (6 visits) of chiropractic care, patients will be randomized to receive either Stratified MC or Standard Chiropractic Care. Stratified MC: patients will complete the MAINTAIN instrument and be stratified to MC or symptom-guided care (clinicians’ judgment). Patients in the Standard Chiropractic Care arm will receive standard treatment based on the chiropractor’s judgment. The primary outcome is the total number of days with activity-limiting pain measured at 12 months. Secondary outcomes include the number of missed working days and loss of work productivity due to pain, pain intensity, disability, health-related quality of life, perceived improvement, and implementation of MAINTAIN instrument outcomes. An intention-to-treat protocol and generalized estimating equations (GEE) linear regression models will be used for analysis.

**Discussion:**

This study investigates the impact of using a clinical instrument to identify patients with recurrent spinal pain to target those who benefit most from a chiropractic MC approach. Strict inclusion criteria should ensure a suitable target group, and frequently collected repeated measures should provide accurate outcome assessment. The study is pragmatic and includes standard clinical procedures facilitating the generalizability and transferability of the results into clinical practice.

**Trial registration:**

ClinicalTrials.gov NCT05350254. Prospectively registered on April 22, 2022, last modified on December 08, 2023. The first patient was randomized into the study on December 21, 2023.

## Introduction

### Background and rationale

Spinal pain, consistingof neck, mid-back, and lower back pain, is a highly prevalent condition [1]. It is considered one of the largest economic health burdens in Western societies [1]. Specifically, low back pain is responsible for more years lived with disability than any other condition in the world, with more than 500 million cases in 2020 [2]. Neck pain affected 203 million people in 2020 [3]. The lifetime prevalence of thoracic pain is between 15.6 and 19.5% [4]. Despite the high overall disability burden for some people, including significant costs for individuals and health care systems, interventions aimed at secondary or tertiary prevention of spinal pain have not been widely evaluated. To date, the few efforts have been focused on the effects of exercise therapy with or without education in the prevention of recurrences or long-term disability [5].

Chiropractic maintenance care (MC) is a long-term management strategy introduced after an initial care plan is successful [6–17]. It is a type of secondary prevention and aims to prevent future episodes and deterioration of the condition by treating patients at pre-planned intervals, regardless of symptoms [6–17]. Chiropractic MC treatment usually includes regularly scheduled manual therapy, individual exercises, and lifestyle advice [18–23]. Historically, it has been reported that patients were mainly selected to receive MC based on their previous history of pain and on the effectiveness of the initial care plan [24–27].

Based on this, a pragmatic randomized clinical trial (RCT) investigated the effectiveness of MC in patients with recurrent and persistent low back pain [16]. Results presented a large variability [17] suggesting that there were sub-groups of patients with better outcomes (fewer days with pain and fewer visits) in the MC arm of the study.

Psychological [28, 29], behavioral [30], and social characteristics [31] of people with spinal pain are known to be important in the transition from acute to recurrent and persistent pain states [32–34]. The bio-psycho-social model is a framework that recognizes the influence of multiple interacting factors from different domains on spinal pain. Although not without limitations, it is the current leading framework guiding the management of spinal pain [31, 35–37]. Based on the cognitive-behavioral conceptualization of pain, the West Haven-Yale Multidimensional Pain Inventory (MPI) was developed to capture and measure the chronic pain experience [38]. The MPI instrument identifies three sub-groups [34] with similar characteristics within each sub-group. This classification has been shown to be reliable, valid, and useful in outcome-based research [39, 40]. The three different sub-groups are adaptive copers (AC; characterized by low pain severity, low interference with everyday life, low life distress, a high activity level and a high perception of life control), interpersonally distressed (ID; who tend to perceive negative responses by significant others to their pain behavior and complaints), and dysfunctional (DYS; characterized by high pain severity, marked interference with everyday life, high affective distress, low perception of life control and low activity levels) [38]. These sub-groups have been used in clinical settings to investigate neck and low back pain [41–43], temporomandibular disorders [44], headaches [45], fibromyalgia [46], and cancer pain [47] and have been associated with different clinical outcomes.

Secondary analyses of the data from the pragmatic RCT [48] revealed that patients in the DYS sub-group reported better outcomes from the MC approach. Specifically, these patients reported 30 fewer days with pain and an equal number of treatments compared to patients in the DYS sub-group who received the control (non-MC) intervention. Comparatively, patients in the ID and AC subgroup allocated to the MC treatment arm reported equal or more days with pain and 1.5 and 3.9 more treatments (respectively) compared to patients in the same MPI sub-group receiving the control intervention.

These results indicate that MC may be best recommended to patients in the DYS sub-group and not recommended to patients in the AC subgroup. Although there is evidence to support the validity and reliability of the MPI instrument, it was not designed to be used in daily clinical practice. Therefore, to apply the above-mentioned research results into clinical practice, the user-friendly MAINTAIN instrument was developed by the previous RCT investigators [49] based on the original MPI instrument.

The conclusions from a previous exploratory factor analysis by Turk and Melzack [50] were used to select which items would be most suitable for a short version of the original instrument. Different scoring algorithms were explored to find an appropriate model with an optimal compromise between diagnostic accuracy and ease of use in clinical settings. Ten questions from the original MPI questionnaire capturing 5 dimensions of the patient’s pain experience: pain severity, interference, life control, affective distress, and support were identified and combined into the MAINTAIN instrument [49]. It takes about 3 min in total for patients to complete and for clinicians to score. The MAINTAIN score ranges from − 12 to 48, and the proportion of a DYS sub-group profile increases with a higher score, whereas the proportion of an AC sub-group profile increases with a lower score.

Based on data collected from three different clinical populations [5] at a threshold of 18, the MAINTAIN instrument has a sensitivity of 95.8% and specificity of 64.3% for the DYS sub-group profile [5, 12, 16]. At a threshold of 22, the MAINTAIN instrument has a sensitivity of 81.1% and a specificity of 79.2% for a positive test for the DYS sub-group profile. Based on these statistics, three categories have been suggested based on MAINTAIN scores: − 12–17 = not a candidate for MC, 18–21 = good candidate for MC, and 22–48 = very good candidate for MC [49].

Despite these encouraging results, the usability and impact of the MAINTAIN instrument applied in clinical practice remain unknown. Therefore, it is fundamental to investigate the outcomes and process of implementing the MAINTAIN instrument into clinical practice.

### Objectives

The overall goal of this randomized clinical trial is to investigate the impact and process of implementing the MAINTAIN instrument in clinical practice to classify patients with spinal pain. The primary aim of this study is to assess the effectiveness and cost-effectiveness of stratified MC guided by the MAINTAIN instrument score compared to standard chiropractic care (without the MAINTAIN instrument). The secondary aim is to assess the fidelity and procedure compliance of implementing the MAINTAIN instrument.

We hypothesize that participants receiving the stratified intervention guided by the MAINTAIN instrument will present better outcomes (e.g., fewer days with activity-limiting pain and lower pain intensity and disability) at 12-months compared to the standard chiropractic care intervention. It is also hypothesized that compliance with procedures to implement the MAINTAIN instrument will be high.

### Trial design

This is a type 1 hybrid effectiveness-implementation study.

## Methods: participants, interventions, and outcomes

### Study setting

Community-based chiropractors located anywhere in Canada will be invited to participate in this study through social media and advertisements shared with members from their professional provincial organizations. All advertisements will have approval by the research ethical board. All participating chiropractors will be trained in patient recruitment and study protocol with pre-recorded videos and a mandatory live webinar training session. The research coordinator will contact participating chiropractors monthly to ensure protocol adherence, participant engagement, and opportunities for potential troubleshooting.

### Eligibility criteria

Inclusion and exclusion criteria for patients to participate in this study are presented in Table 1.

**Table 1 Tab1:** Eligibility criteria

Inclusion criteria	Exclusion criteria
• Age 18–65 years • Neck pain, mid-back pain, and/or low back pain with or without arm or leg pain for more than 30 days during the past year • Previous spinal pain episodes • No chiropractic care in the past 3 months • Access to a mobile phone and email • Ability to send and receive SMS (text messages)	• Pregnancy • Serious pathology (i.e., acute trauma, cancer, infection, cauda equina syndrome, osteoporosis, vertebral fractures) • Contraindications to manual therapy • Patients with specific spine conditions, such as radiculopathy and spinal stenosis

These criteria will be assessed at the first visit self-reported by patients (all inclusion criteria and pregnancy status) and by clinicians (serious pathology, specific conditions, and contraindications to manual therapy). Final eligibility will be determined by clinicians during the first visit, prior to randomization.

### Study procedure

The general flow of this trial is shown in Fig. 1. At each participating chiropractic office, consecutive patients that meet the eligibility criteria (Table 1) will be invited to participate in the study by the office’s front desk or by the chiropractor (whatever works best for their office) when they call to book their appointment. The invitation of consecutive patients was reinforced in the mandatory webinar training. Eligible patients who agree to participate in the study will be asked to arrive at the office for their first chiropractic and study visit about 30 min before their appointment to get details about the study via an introductory video and study information letter and to sign an informed consent electronically. Patients not meeting the eligibility criteria or choosing not to participate in the study will have no change in the care provided by their chiropractor.

**Fig. 1 Fig1:**
[figure not shown]
Study flow and intervention arms

At their first visit prior to their appointment, participating patients will complete the first electronic questionnaire in REDCap (Questionnaire 0-patient), which includes the MAINTAIN instrument. Once patients complete Questionnaire 0-patient, their chiropractor will examine patients to determine final eligibility and complete Questionnaire 0-clinician also in REDCap.

### Randomization

Participants will be randomly allocated to one of the two intervention arms at the first visit, as part of Questionnaire 0-clinician (immediately after eligibility criteria confirmation): Stratified Maintenance Care (SMC) or Standard Chiropractic Care (SCC), with the number of individuals equally balanced between groups. Central randomization will be performed, using block randomization stratified by clinician, performed by the study biostatistician ([name]) using SAS software. To ensure the allocation sequence is concealed from the researchers and participating clinics, varying block sizes of 2, 4, and 6 will be used. The unique randomization orders will be uploaded into REDCap (Research Electronic Data Capture system, Vanderbilt University, Tennessee) [51]. Each chiropractor will indicate, in their Questionnaire 0-clinician, the number of the patient (i.e., first patient enrolled = #1; second patient enrolled = #2, etc.), which will reveal that patient's group allocation. Importantly, chiropractors will only have access to the MAINTAIN instrument score for patients allocated to the MC group.

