### Sample size

There will be one primary comparison between the two study arms (SMC vs SCC) and a secondary comparison between those classified as DYS across study arms, anticipating that approximately half of each study arm will be classified as DYS. Based on the previous study [17], to detect a difference in the number of days with pain over 12 months [17] between the two main study arms corresponding to a medium Cohen’s effect size of 0.5, with an α-level of 0.05, power of 0.80, a sample consisting of 90 patients per arm would be required. Given that our study includes 2 arms and to account for potential dropouts (20%), our goal will be to recruit 220 patients [52]. Therefore, 15 clinicians will be recruited to collect data from 15 patients each.

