### Data analysis plan

#### Primary outcome

An intention-to-treat protocol will be used, and estimates will be reported with arithmetic means and 95% confidence intervals. The primary outcome (number of days with activity-limiting pain) will be analyzed similar to Eklund et al. (2018,2019) [17, 48]. The number of days with activity-limiting pain will be modeled using generalized estimating equations (GEE) linear regression, using appropriate correlation structure and robust variance estimator. Terms for study arm, time, and study arm by time interaction will be included. A term for MC candidate (yes or no) will be added to this model to investigate stratification and its relationship to outcomes further.

Following a previous study that conducted a similar analysis [16], cost-effectiveness will be investigated both from the health care and societal perspectives. In the health care perspective only costs directly associated with the intervention will be included whereas in the societal perspective all available costs, direct and indirect modeled production loss costs, will be used. Direct medical costs considered in the study are treatment costs (treatment fee) and time loss during treatment and travel (an average time for travel is estimated and added to an average patient visit time). Indirect costs, such as production loss, will be estimated using the human capital approach, where lost time is valued using the hourly wage [65]. Since the data collection is performed between 2023 and 2025, all costs will be adjusted for inflation using a 3 to 5% inflation rate, with the baseline year of the study as a base year [66] and calculated in CAD$. Intervention effectiveness will be estimated by the primary outcome “number of days with a bothersome spinal pain” and self-rated health (EQ5D) as a secondary outcome. The results will be reported as cost-effectiveness planes, cost acceptability curves, and incremental cost-effectiveness ratios (ICER) where the extra cost per extra unit of health effect will be estimated for days with bothersome pain and quality-adjusted life years (QALYs). No interim analyses are planned for this study.

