#### Secondary outcomes

The secondary outcomes will be analyzed and reported independently of the primary outcome. Missed workdays due to pain, loss of work productivity due to pain, pain intensity, global perceived change, self-reported activity limitation, self-rated health, and pain self-efficacy will be reported with arithmetic means and 95% confidence intervals, and GEE linear regression models will be used.

Qualitative interviews data will be analyzed using interpretive description. An inductive approach to thematic analysis will be used to facilitate coding of the data driven by the responses rather than preconceived theoretical or analytical knowledge. Transcripts will be coded, and key themes will be identified. Several well-established techniques to ensure methodological rigor and trustworthiness for interpretive description will be used, including member checking (participants’ comments on any developed themes), verification (researchers converge on recognizing “identical patterns” in the data), referential adequacy (providing enough quotes to ensure the findings fit the data), maintaining an audit trail (records of decisions made), and maintaining a reflexive journal (to help the interviewers identify how their experience may influence the study results).

The RE-AIM framework will be used to assess the impact and implementation of the MAINTAIN instrument using other qualitative and quantitative analyses, see Appendix 1 summary table.

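### Randomisation is blocked within clinician, but the listed terms of the primary GEE omit clinician and the cluster unit is not stated

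*Protocol article*

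**What the plan says.** The Randomization section of the protocol article states: "Central randomization will be performed, using block randomization stratified by clinician". Block sizes are 2, 4 and 6, and the arms are to be the same size ("with the number of individuals equally balanced between groups"). The Sample size section plans 15 clinicians with 15 patients each.

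The Data analysis plan, under Primary outcome, specifies a linear GEE "using appropriate correlation structure and robust variance estimator" and then lists its terms: "Terms for study arm, time, and study arm by time interaction will be included". The next sentence reads "A term for MC candidate (yes or no) will be added to this model to investigate stratification and its relationship to outcomes further". Clinician appears neither as a term nor as a cluster level. Under Secondary outcomes, the measures "will be reported with arithmetic means and 95% confidence intervals, and GEE linear regression models will be used", with no terms given.

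On baseline data, the Study procedure section says that at the first visit "participating patients will complete the first electronic questionnaire in REDCap (Questionnaire 0-patient), which includes the MAINTAIN instrument". Table 2 shows that pain NRS, disability, EQ-5D-5L and self-efficacy are collected in the same questionnaire. Allocation is revealed afterwards, in the clinician's own Questionnaire 0.

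**The concern.** When allocation is balanced within each clinician, differences between clinicians largely cancel out of the arm comparison. A model without clinician still counts those differences as error, so its standard error is larger than the true sampling variation. A clinician effect is plausible here. Initial care is tailored by each clinician, and control care may or may not include maintenance care according to that clinician's usual practice.

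The unnamed cluster unit makes this worse, because the two natural readings err in opposite directions. As worded, the plan permits a slightly conservative or a slightly liberal primary test.

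Baseline covariates are a related point. The primary outcome is collected by SMS only after Questionnaire 0, so it has no baseline value of its own. The MAINTAIN score and pain NRS are the natural substitutes, and every patient gives them before allocation.

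**Working it through.** **Inputs.** From the article: 1:1 allocation blocked within clinician; 15 clinicians × 15 patients = 225; 20% dropout, so 15 × 12 = 180 completers, or 90 per arm; standardised difference 0.5 ("corresponding to a medium Cohen’s effect size of 0.5"); α 0.05, taken as two-sided. The article gives no ICC and no correlation between baseline measures and the outcome, so both are assumed over a range.

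**The plan's own figure.** A difference of 0.5 SD at two-sided 0.05 and power 0.80 needs 63 per arm (64 by t-test), not the stated 90. At 90 per arm the power is 0.918. That mismatch is a separate matter. It does not affect the ratios below, and 90 per arm is used only to express them as power.

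**Step 1: GEE clustered on patients, clinician omitted.** Let σ² be the total variance of a patient's 12-month summary and N the number of patients.
- The variance assumed without clinician is about 4σ²/N.
- The true variance under within-clinician balance is about 4σ²(1 − ICC)/N.
- The ratio of interval widths is therefore 1/√(1 − ICC).
- The actual type I error is 2[1 − Φ(1.96/√(1 − ICC))].

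| Assumed ICC | Width ratio | Type I error | Power, clinician omitted | Power, clinician included |
|---|---|---|---|---|
| 0.01 | 1.005 | 0.049 | 0.919 | 0.921 |
| 0.03 | 1.015 | 0.047 | 0.922 | 0.926 |
| 0.05 | 1.026 | 0.044 | 0.924 | 0.931 |
| 0.10 | 1.054 | 0.039 | 0.929 | 0.942 |

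**Step 2: simulation.** The set-up was 15 clinicians × 12 completers, blocks of 2, 4 and 6, one summary value per patient, no treatment effect and 3,000 runs per ICC.

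| ICC | SE, patient-level robust | SE, clinician fixed effects | Width ratio | Rejection, patient-level robust | Rejection, robust clustered on clinician |
|---|---|---|---|---|---|
| 0 | 0.1478 | 0.1490 | 0.992 | 0.046 | 0.062 |
| 0.03 | 0.1478 | 0.1468 | 1.007 | 0.047 | 0.067 |
| 0.05 | 0.1480 | 0.1455 | 1.017 | 0.053 | 0.074 |
| 0.10 | 0.1476 | 0.1415 | 1.043 | 0.038 | 0.068 |

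The gains are a little smaller than the formula gives, and at ICC 0 there is none. The Monte Carlo error of a 5% rejection rate is √(0.05 × 0.95/3000) = 0.004. The 0.053 at ICC 0.05 comes from a batch in which the fixed-effects analysis also ran high (0.055), so it reads as noise and not as a contrary finding.

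**Step 3: robust variance clustered on clinician.** The last column uses the uncorrected sandwich estimator with a normal critical value. With 15 clusters it rejects too often at every ICC tried. At ICC 0.10 its mean SE was 0.1396, against 0.1476 for the patient-level version, so the intervals are not too wide in this case.

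**Step 4: baseline covariates.** Omitting a covariate with correlation r to the outcome multiplies the interval width by 1/√(1 − r²):
- r = 0.3: 1/√0.91 = 1.048
- r = 0.5: 1/√0.75 = 1.155
- r = 0.6: 1/√0.64 = 1.250

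**The case against.** The strongest reply is that this is a condensed article with no analysis plan shown. Covariate choice is normally settled in that plan, the listed terms are not declared exhaustive, and the analysis is said to follow earlier trial reports that are not at hand. This stands for the prognostic covariates: their absence is no error, and adding them is a recommendation. It stands only in part for clinician. The article prints the model's terms, and that list lacks the factor by which randomisation was restricted.

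The second reply concerns size. At plausible ICCs the effect of omitting clinician is small, and with patient-level clustering the error is conservative. An unadjusted comparison of randomised arms remains valid. All of this is correct.

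Three stronger readings are tempting, and the documents do not support them.
- A reader might infer that the model ignores every baseline variable. The article adds a maintenance-care candidate term, and candidacy is defined by the MAINTAIN score, which is collected at baseline. That term reads as a further analysis, and the article does not say which MAINTAIN measurement defines it, but a claim that nothing is used would be wrong.
- A reader might infer that the intervals are certainly too wide. That needs patient-level clustering and a non-zero ICC, and the article states neither.
- A reader might turn the covariate gain into wasted patients: 1/(1 − 0.09) = 1.10 to 1/(1 − 0.36) = 1.56 times the sample. Those multiples rest wholly on the assumed r, and no figure in the article supports one.

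**Conclusion.** The point holds as a modest defect of specification. The stated primary model does not carry the only stratification factor, and the cluster unit is left open.

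- With patient-level clustering, the intervals are about 0.5% to 5% too wide for assumed ICCs of 0.01 to 0.10. Type I error falls to about 0.04 at the top of that range, and the loss of power at 90 per arm is at most about 1.3 percentage points (0.942 − 0.929).
- With clustering on about 15 clinicians and no small-sample correction, the intervals are slightly too narrow, with simulated type I error of 0.062 to 0.074.

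These figures assume a clinician effect common to both arms and one summary value per patient. Baseline covariates may offer the larger gain, but its size depends on correlations that the article does not give.

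**What to change.** **Primary outcome.** Add clinician as a fixed effect to the primary GEE and name the patient as the cluster unit. If the team prefers to cluster on clinician, specify a small-sample correction. Prespecify the Questionnaire 0 MAINTAIN score and Questionnaire 0 pain NRS as covariates, and report the model without these two covariates as a sensitivity analysis. State that the maintenance-care candidate term is a further analysis, and say which MAINTAIN measurement defines it.

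**Secondary outcomes.** Add clinician to each model. Use a baseline value only where Table 2 provides one: pain, disability, EQ-5D and self-efficacy. Missed workdays, productivity loss and global perceived change have none. Appendix 1 lists T0 among the GEE time points for the first four, so baseline should enter either as a covariate or as a T0 response, not both.

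**Cost.** Plan wording only. The variables are already collected, recruitment runs to May 2026 and analysis is scheduled for fall 2027, so the change can be fixed before any outcome comparison is made.
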